#### 2.2.2. Sample Size

The sample size was calculated based on the results obtained by Citak et al. [35], using the Female Sexual Function Index (FSFI) scores as a reference and the statistical program GRANMO 8.0 (Datarus, Barcelona, Spain). Assuming a two-tailed test with an alpha risk of 0.05 and a statistical power greater than 0.8, 62 participants per group will be required to detect a difference of 2.4 points or greater. A common standard deviation of 4.5 was assumed. Additionally, a 10% dropout rate was accounted for in the estimation.

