
To assess the safety of the interventions, in all treatment sessions, the physiotherapists performing the treatments (PT3 and PT4) will record any potential incidents, such as discomfort, increased pain, use of medication, need for additional medical consultations, postponement, or suspension of treatment due to possible adverse effects of the interventions.

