#### 2.2.6. Statistical Data Analyses

A descriptive analysis of each collected variable will be conducted. For continuous variables, means, medians, standard deviations, and quartiles will be calculated, depending on whether the assumption of normality is met, as determined beforehand using the Shapiro–Wilk test. Qualitative variables will be described with absolute and relative frequencies in percentages.

For intragroup comparisons over time (A0–A4), if continuous variables follow a normal distribution, repeated-measures ANOVA will be used. If the data do not follow a normal distribution, the Friedman test will be used. For ordinal variables (FSFI, PFDI-20, PFIQ-7, Broome Scale), the Friedman test will be used for comparisons across more than two time points, or the Wilcoxon signed-rank test for comparisons between two time points, regardless of whether they follow a normal distribution. For dichotomous variables, the McNemar test will be applied for two time points, and the Cochran Q test will be used for multiple time points.

To determine the association between groups at each time point, a dichotomous independent variable and a quantitative dependent variable with a parametric distribution, the independent Student’s t-test will be used if the data follow a parametric distribution. If the assumption of normality is violated, the Mann–Whitney U test will be applied. For ordinal variables, the Mann–Whitney U test will be used to compare two independent groups, and the Kruskal–Wallis test will be applied for comparisons across more than two groups. For dichotomous variables, the Chi-square test will be used, and Fisher’s exact test will be applied if the expected frequency is less than 5. The effect will be assessed by the difference in means, and the precision will be measured using the 95% confidence interval.

The main analysis to compare the groups will be adjusted to the baseline pre-intervention values of the outcome variables. In all cases, a significant level of *p* < 0.05 will be used. The statistical software SPSS, version 29, IBM, will be employed.

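### The between-group tests named for each visit ignore a woman's earlier post-treatment values, so the A2–A4 comparisons of FSFI and VAS can be biased if loss depends on response differently by arm; one longitudinal mixed model would guard against this

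*Protocol article*

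**What the plan says.** Section 2.2.6 introduces the between-group analysis with "To determine the association between groups at each time point, a dichotomous independent variable and a quantitative dependent variable with a parametric distribution". It then names the independent t-test for normally distributed data and Mann–Whitney otherwise. FSFI is listed among the ordinal variables, so its named test is Mann–Whitney. The effect is to be a difference in means with a 95% confidence interval. One further sentence says that the main group comparison will be adjusted for the pre-intervention values; no model is named.

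Four other statements bear on the point:
- Section 2.2.2 expects loss: "Additionally, a 10% dropout rate was accounted for in the estimation".
- Section 2.1 says that participants are not blinded.
- Section 2.2.4 places follow-up at 3, 6 and 12 months after treatment (A2, A3, A4) and provides for reminders and rebooking of missed assessments.
- Section 2.2.3 says that FSFI is completed online from a form sent by email after each assessment.

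**The concern.** A test run separately at A4 sees only the women with an A4 value. A woman who gave values at A1 and A2 and then left contributes nothing to it, although her earlier values may say a good deal about why she left and what her A4 value would have been. Adjustment for A0 covers loss that baseline explains. It does not cover loss that depends on how she responded to treatment.

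Participants know their arm, and the article itself (section 3.1) expects the radiofrequency arm to do better, so reasons to leave could differ between arms. If poor responders leave the control arm more readily, the remaining controls look too good and a radiofrequency effect is understated. The reverse pattern overstates it. The allowance in the sample size protects precision and has no bearing on who leaves. At stake are the longer-term comparisons of both primary outcomes, and section 4 counts the one-year follow-up among the study's strengths.

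**Working it through.** **1. The plan's own figure.** Inputs from section 2.2.2: two-sided alpha 0.05, power 0.80, SD 4.5 in both arms, and the result to be reproduced, "62 participants per group will be required to detect a difference of 2.4 points or greater".

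n per arm = 2 × (1.960 + 0.842)² × 4.5² / 2.4² = 55.2. Allowing for 10% loss, 55.2 / 0.9 = 61.3, so 62. (Rounding up to 56 first gives 56 / 0.9 = 62.2, so 63.) The stated 62 reproduces. After 10% loss, 62 × 0.9 = 55.8, about 56 per arm, and an unadjusted comparison has about 80% power. Loss is therefore covered for power.

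**2. When bias arises.** In one arm, observed mean − full mean = share lost × (mean of stayers − mean of leavers). If share and gap are the same in both arms, the two terms cancel. If they differ, the difference enters the estimate.

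**3. Illustration.** From the article: 62 per arm, SD 4.5, true difference 2.4, 10% loss. Assumed, because the article gives none of these: all loss occurs after A1; 10% is lost in each arm; control leavers are those with the worst A1 scores; radiofrequency leavers are random; A0 correlates 0.5 with A1 and with A4; A1–A4 correlation is 0.6 to 0.75.

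- Removing the lowest 10% of a normal distribution raises the stayers' mean by 0.1755 / 0.9 = 0.195 SD. At A1 that is 0.195 × 4.5 = 0.877 points.
- The control A4 mean rises by 0.6 × 0.877 = 0.526 to 0.75 × 0.877 = 0.658.
- Baseline adjustment takes back slope × rise in A0 = 0.5 × (0.5 × 0.877) = 0.219.
- Bias left: 0.307 to 0.439. Adjusted estimate: 2.4 − 0.307 = 2.09 to 2.4 − 0.439 = 1.96.
- Residual SD = 4.5 × √(1 − 0.5²) = 3.90. Standard error with 56 per arm = 3.90 × √(2/56) = 0.736.
- Power for 2.4 (ratio 3.26): about 90%. For 2.09: about 80%. For 1.96: about 75%.
- With no true effect, a shift of 0.307 to 0.439 against that standard error gives two-sided rejection of about 7% to 9%. In this scenario the excess false positives favour the control arm.

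**4. Simulation.** I ran 4,000 trials per scenario with six lost per arm. Control leavers were chosen either exactly on A1 or on A1 plus noise of half an SD.

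| Loss | Baseline-adjusted completers | Power | Null rejection | Likelihood estimate using A0 and A1 |
|---|---|---|---|---|
| Poor A1, controls only | 1.96–2.13 | 77–82% | 6–9% | 2.38–2.39 |
| Random, or same A1-dependence in both arms | 2.39–2.41 | 89–91% | 5–6% | 2.39–2.41 |

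Allowing for other selection strengths and simulation error, the range for the first row is about 1.95–2.15, with power about 75–83% and null rejection about 6–9%. VAS was not simulated, because the article gives no SD or target difference for the group comparison. The mechanism is the same.

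**The case against.** The strongest objection is that this is a missing-data policy left unwritten, and a journal article may leave that to the full protocol or SAP. The article does not say that only attenders are analysed. The named tests, or an adjusted model, could be run on imputed data. That stands: observed-case analysis is inferred from the tests, and the lack of an analysis population or imputation rule is not held against the plan. What remains is that the article does fix a method for between-group comparison, and a visit-by-visit test cannot itself use a woman's earlier post-treatment values.

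The second objection is that the illustrated mechanism is severe. Exact selection puts control leavers about 1.95 SD below stayers at A1 (0.1755 / 0.1 + 0.195), while radiofrequency loss is wholly random. With a gap of about 1 SD in controls only, the adjusted estimate is 2.17–2.25, power 84–86% and null rejection 5–6%. Controls also receive 12 sessions of active treatment, and missed assessments are rebooked, so strong arm-specific loss may not occur. This stands too and limits the size of the claim.

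A reader might infer more in two places, and the article does not support either reading:
- Section 2.2.5 lists "need for additional medical consultations, postponement, or suspension of treatment due to possible adverse effects of the interventions". This is an incident to be recorded. Nothing says that such women leave follow-up or the analysis, so it is not a second source of missing outcomes.
- Section 2.2.6 also says "For intragroup comparisons over time (A0–A4), if continuous variables follow a normal distribution, repeated-measures ANOVA will be used". In standard form that method, like Friedman and Cochran Q, drops anyone with a missing visit. It serves comparisons within a group over time and does not decide the comparison between arms.

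**Conclusion.** The point holds as a conditional one. The named per-visit tests leave the A2–A4 comparisons of FSFI and VAS open to bias if loss depends on earlier response differently by arm. It would go too far to say that the plan does bias these comparisons: the article gives no loss by arm and no reasons for leaving, and the bias is zero if loss is random or depends on A1 alike in both arms.

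Under the assumed control-only mechanism, the baseline-adjusted analysis loses about 0.25 to 0.45 of the 2.4 points, and power falls from about 90% to about 75–83%. Even then it stays near the design's own target of "a statistical power greater than 0.8". The figures rest on the assumed correlations, on selection by A1, and on reading the unnamed baseline-adjusted model as a completer analysis of covariance. The case for change is that a better method exists for data the trial will already hold, and that it loses essentially nothing when loss is benign.

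**What to change.** In section 2.2.6, make the main between-group analysis of FSFI and VAS one mixed model for repeated measures. Fit it to all randomised women in their allocated arm, using all available A1–A4 values. Include the baseline value, visit, group and group-by-visit, with an unstructured covariance. Report the adjusted mean difference and 95% confidence interval at each visit. Keep the named t-test and Mann–Whitney comparisons as sensitivity analyses. This also supplies the model that the baseline-adjusted sentence leaves unnamed.

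The cost is wording and slightly more analysis work; SPSS 29, already specified, fits the model. No change to sample size, visits or data collection is needed. The model relies on a missing-at-random assumption, which is weaker than what the completer tests need but still cannot be verified. It also treats FSFI as a continuous score, as the sample-size calculation and the planned difference in means already do.

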#### 2.2.3. Physiotherapy Assessments

Physiotherapy assessments will be conducted by a physiotherapist specializing in Pelvic and Women’s Health (PT1) with over 10 years of experience, who will be blinded to the participants’ intervention group. The physiotherapy assessment will include an interview to collect socio-demographic and clinical history data, as well as a physical examination (Table 1). The outcome variables of the study that will be collected at all assessments are as follows:Primary outcomes:
(1)Pelvic pain: The perceived pain intensity will be measured using the Visual Analog Scale (VAS). This scale consists of a 100 mm horizontal line, where the participant marks the intensity of their pain, with the left margin of the line representing “no pain” and the right margin representing “the worst possible pain.” A minimum detectable change (MDC) of 15 mm is required for clinical significance [36].(2)Female sexual function: The Spanish version of the FSFI will be used [37]. The FSFI questionnaire has a scoring range from 2 to 36 points, with higher scores indicating better sexual function. It assesses six domains: desire, arousal, lubrication, orgasm, satisfaction, and pain. A change of 6 points will be considered clinically relevant [38].Secondary outcomes:

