#### 2.2.4. Follow-Up

Assessments will be conducted at four time points by the same blinded physiotherapist (PT1): before the intervention (A0), after the physiotherapy intervention (A1), and at three follow-ups, 3-, 6- and 12- months post-treatment (A2, A3, and A4, respectively).

The assessment appointment will be scheduled with them, and a reminder will be sent via SMS and email. If they are unable to attend, they will have access to a phone number and email address to contact, and another appointment will be scheduled with them.

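### Two unranked primary outcomes, four post-treatment visits and a blanket p < 0.05 leave the primary claim without a defined test that holds the planned 5% error rate

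*Protocol article*

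**What the plan says.** Section 2.2.3 opens its list with "The outcome variables of the study that will be collected at all assessments are as follows:Primary outcomes" and then gives VAS pain first and FSFI second, with no ranking. Section 2.2.4 and Table 1 set one baseline visit (A0) and four post-treatment visits: A1 after treatment, and A2, A3 and A4 at 3, 6 and 12 months.

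Section 2.2.6 gives repeated-measures ANOVA and the Friedman test to within-group change only. The between-group tests are introduced by "To determine the association between groups at each time point". The section then says that the main group comparison is adjusted for baseline values, without naming a visit or an outcome order. It ends on the level: "In all cases, a significant level of *p* < 0.05 will be used".

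Section 2.2.2 sizes the trial "using the Female Sexual Function Index (FSFI) scores as a reference". It reads "Assuming a two-tailed test with an alpha risk of 0.05 and a statistical power greater than 0.8, 62 participants per group will be required". The target is 2.4 FSFI points, and the section adds "A common standard deviation of 4.5 was assumed". No visit is attached to this calculation.

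**The concern.** The sample size spends the whole 5% on one comparison of one outcome. The analysis section offers up to eight primary between-group comparisons, each at 5%. No overall between-group test stands in front of them, and nothing says which one decides the trial. A claim that radiofrequency works could therefore rest on whichever outcome and visit crosses 0.05.

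This matters because the Discussion ties wide implementation to the combined treatment being shown effective, and notes the added cost of the technology. Both primary outcomes are self-reported and participants are not blinded, so a free choice among tests would be a weak basis for that step.

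**Working it through.** **1. The plan's own figure.** Inputs from section 2.2.2: difference 2.4, SD 4.5, two-sided alpha 0.05, power 0.80, dropout 10%.

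- Normal approximation: n = 2 × (1.960 + 0.842)² × 4.5² / 2.4² = 55.2, so 56 per group (56.2 unrounded with the t distribution).
- Dropout: 56 × 1.10 = 61.6, so 62; or 56 / 0.90 = 62.2, so 63.

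The stated 62 per group is reproduced. It is the size for one FSFI test with full alpha.

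**2. Number of primary comparisons.** Two outcomes × four post-treatment visits = 8, if the visit-wise tests are read as primary.

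**3. Upper reference, independent tests.**

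- Either direction: 1 − 0.95⁸ = 33.7%.
- Favouring radiofrequency only: 1 − 0.975⁸ = 18.3%.

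**4. Correlated tests.** The article gives no correlations, so these are assumed. Eight standard normal statistics were simulated with no effect on either outcome at any visit (400,000 draws, cut-off 1.96). The correlation was equal between all visits and constant between the outcomes.

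| Between-visit r | Between-outcome r | At least one of 8, two-sided | At least one favouring radiofrequency | Both outcomes at the same visit |
|---|---|---|---|---|
| 0 | 0 | 34% | 18% | 1.0% |
| 0.3 | 0.2 | 31% | 16% | 1.4% |
| 0.5 | 0.4 | 28% | 14% | 2.4% |
| 0.7 | 0.4 | 23% | 12% | 2.1% |
| 0.8 | 0.6 | 19% | 10% | 3.2% |
| 0.9 | 0.7 | 15% | 8% | 3.4% |

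A correlation that decays with time between visits raises the two-sided figures by one to two points where the tests are correlated. The range over the whole grid stays 15–34%.

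**5. Smaller families.**

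- FSFI alone at four visits: 9–17% for between-visit correlations of 0.9 to 0.3.
- Both outcomes at one visit: 1 − 0.95² = 9.8% if independent, 8.3% at correlation 0.7.

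Fixing only the outcome or only the visit therefore does not restore 5%.

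**6. What splitting alpha would cost**, with the FSFI inputs from step 1.

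- One visit, 0.025 per outcome: 67 evaluable per group, 75 with dropout. The planned 56 evaluable give about 72% power.
- Bonferroni over eight tests (0.00625): 90 evaluable per group, 100 with dropout. The planned 56 give about 53% power.

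**The case against.** The strongest reply is that the article states no decision rule. A reader might infer from section 2.2.6 that any of eight tests may be claimed as success, and that the error rate is therefore 20–30% as a matter of fact. The documents do not support that much. Where the article describes success, in the hypothesis and at the end of the Discussion, it joins pain and sexual function. If both had to be significant at the same visit, the error with no effect on either outcome would be only about 1–3%. That rule is not stated either, however. Under it, if one outcome truly improved, the free choice of visit could still raise the error on the other towards the 9–17% of step 5.

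The main analysis sentence is a second reply. It may mean one model rather than a series of visit-wise tests, so eight tests is a reading and not a stated count. But the sentence names no visit and no outcome, so it does not settle the matter.

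A third reply is that sizing on FSFI makes it the real primary outcome. The text never says so. Pain is listed first and is the entry criterion, and the choice among four visits would remain.

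Finally, an analysis plan that is not shown may settle visit and order. Ordinary detail can be left there. Here, though, the article is not silent: it sets the unadjusted level for every test, and a plan with an adjustment would have to contradict it. The sample size also needs a visit to be interpretable.

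Section 2.2.4 announces four time points and lists five. That is a clerical slip with no bearing on the error rate, since the abstract and Table 1 give the schedule correctly.

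**Conclusion.** The point stands as an undefined primary test combined with a stated significance rule that does not secure the 5% used in the sample size.

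The size is conditional. If either outcome at any visit counts as success, the two-sided error is about 15–34%, and about 19–31% for between-visit correlations of 0.8 to 0.3. For errors favouring radiofrequency it is about 8–18%, against 2.5% for a single two-sided 5% test. Two outcomes at one named visit would still give 8–10%. These figures rest on assumed correlations and on no effect on either outcome at any visit. They are not error rates that the article itself fixes.

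**What to change.** Before any unblinded data are seen, state in sections 2.2.3 and 2.2.6:

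- one primary visit for the baseline-adjusted between-group comparison;
- one rule for the two primary outcomes that holds 5% overall;
- a reworded significance sentence that applies 0.05 within that rule and not to every test.

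Section 2.2.2 should then name the same visit.

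One workable choice is a fixed sequence: FSFI first, for example at A1, then VAS pain at the same visit only if FSFI is significant. FSFI keeps its full alpha and the planned 62 per group. The authors may prefer another visit, or pain first, given that the trial enrols on pain; power for a first test of pain would then need its own calculation. They may also require both outcomes at the named visit. That needs no alpha adjustment but costs power: with 80% for each outcome and independence (both assumed), 0.80² = 64%.

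Report the other visits and outcomes as secondary, with 95% confidence intervals. Correct the visit count in section 2.2.4 in passing.

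The cost is a few sentences and, for the FSFI-first sequence, no change in sample size. The real downside is that results at other visits, including 12 months, or on the second outcome after a failed first test, cannot carry the confirmatory claim.

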### 2.3. Qualitative Study

A qualitative study will be conducted from a phenomenological paradigm to know the postpartum women’s experience with adherence to the advice and home exercises recommended by their physiotherapist. The consolidated criteria for reporting qualitative research (COREQ) will be followed [47].

#### 2.3.1. Research Teams and Reflexibility

The individual interviews and focus groups will be conducted by two physiotherapists specialized in Pelvic and Women’s Health, who are women, mothers, university professors, and hold a PhD. Interviewer 1 (PT1) will be familiar with the participants in advance, as she is the blinded evaluator of the RCT. This evaluator will interview the women who have already completed the follow-up in order to avoid conflicts related to the potential disclosure of the intervention group during the interviews. Interviewer 2 (PT2) will not know the participants in advance and will conduct interviews with women who are between the A2 and A4 follow-up assessments. Both evaluators have prior experience conducting individual interviews and focus groups within the framework of qualitative studies in women’s health.

#### 2.3.2. Qualitative Study Design

The theoretical framework and methodological orientation for the qualitative part of the RASDOP study is based on phenomenology. The main objective will be to understand the experience of postpartum women in adhering to a physiotherapy treatment aimed at improving their postpartum pelvic pain.

Women who have completed the 12 individual physiotherapy sessions will be included, regardless of the assigned treatment group of the RCT. Women will be divided into two groups: one consisting of women who are in the follow-up period (3 to 12 months after completing the intervention), or those who have already finished their participation in the study (> 12 months after the physiotherapy intervention). The recruitment will be consecutive, and the study will end when data saturation is reached. Data saturation will be deemed achieved when the information gathered aligns with that from earlier interviews.

All interviews will be conducted face-to-face and will take place in a classroom in the Nursing and Physiotherapy Building at the University of Alcalá, near the FPSM Research Group laboratory. The focus groups will consist of four to six women who do not know each other beforehand. In the interviews, only the participating postpartum women and one of the interviewers (PT1 or PT2) will be present. The interviewers will use a pre-designed question guide (Table 3), and the sessions will be audio-recorded with the prior consent of the participants.

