
The long-term maintenance of positive outcomes depends not only on the treatment but also on behavioral changes and adherence to the physiotherapist’s recommendations [31]. Therefore, exploring and understanding women’s motivation, perceived self-efficacy, and expectations, among other factors, seems essential to ensuring the long-term effectiveness of conservative treatments [32].

The RASDOP study is designed to (i) compare standard multimodal physiotherapy for postpartum pelvic pain with an experimental approach that includes radiofrequency therapy, whose efficacy and safety remain unknown; and (ii) explore factors influencing therapeutic adherence and perceived self-efficacy, identifying the challenges and facilitators that affect postpartum women in adopting and maintaining recommended practices for long-term benefits.

Our hypothesis is that the inclusion of radiofrequency within a multimodal physiotherapy treatment enhances its efficacy in managing postpartum pelvic pain by reducing pain, improving sexual function, eliminating the presence of MPS in the PFM, and improving PFM qualities. Additionally, factors influencing postpartum women’s adherence or non-adherence to a conservative treatment plan for pelvic pain will be explored. These findings will assist clinicians in decision-making regarding the inclusion of technologies such as radiofrequency in the management of pain in this population and provide insights to guide the development of a biopsychosocial approach to postpartum pain treatment.

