## Figures and Tables

**Figure 1 jcm-14-01489-f001:**
[figure not shown]
CONSORT follow Diagram. FPSM-RG: Physiotherapy in Women’s Health Research Group, A: assessment; IC: informed consent; MP-G: multimodal physiotherapy group; RMP-G: radiofrequency + multimodal physiotherapy group; PFMT: pelvic floor muscle training.

**Table 3 jcm-14-01489-t003:** Proposed interview guide for the RASDOP study.

Number	Questions
1.	What has been your experience participating in this physiotherapy program?
2.	What motivated you to participate in this physiotherapy program? What were your goals or objectives? What did you aim to achieve? Do you think you have achieved them?
3.	From your perspective, what aspects have made it difficult to achieve the goals or objectives of this program? How could we have supported you better?
4.	Was it easy or difficult for you to attend the treatment and evaluation sessions? Why? Have we made it easier for you in any way? Is there anything that could have made it even easier?
5.	Have you been able to apply the knowledge gained during the treatment or evaluation sessions? What facilitated this? What made it more difficult?
6.	Have you adopted or modified any habits that you believe have improved your pelvic health? What about other aspects of your general health? Which ones? Was it easy to adopt these habits? Why? Was it difficult? Why?
7.	Do you believe that attending pelvic floor physiotherapy has been important for your recovery? Why? Do you think you would have needed any other treatments, guidance, advice, or modifications to the program? Are there any treatments, guidance, or advice that you consider unnecessary?
8.	What were and are your expectations regarding the improvement in pelvic pain? Do you think you have done or are doing anything to help alleviate it? Do you feel that you need or would have needed anything else?
9.	Do you think there is anything more or different we could do to help women experiencing pelvic and/or perineal pain postpartum?

The first question from each numbered set will be asked. Follow-up questions will be posed as needed based on the flow of the interview.

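### The qualitative study's entry rule (all 12 sessions completed) shuts out women who missed or stopped supervised treatment, although its aim covers non-adherence to that treatment

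*Protocol article*

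**What the plan says.** Section 2.3.2 of the protocol article gives the eligibility rule in one sentence: "Women who have completed the 12 individual physiotherapy sessions will be included", whichever trial arm they were in. It then names two sampled groups, both placed in time by the intervention. The first is "one consisting of women who are in the follow-up period (3 to 12 months after completing the intervention"; the second is women more than 12 months past it. On sampling it says: "The recruitment will be consecutive, and the study will end when data saturation is reached". No route is described for a woman who began treatment and did not finish it.

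The same section gives the main objective as to "understand the experience of postpartum women in adhering to a physiotherapy treatment aimed at improving their postpartum pelvic pain". The Introduction goes further and names the negative case: "factors influencing postpartum women’s adherence or non-adherence to a conservative treatment plan for pelvic pain will be explored". The Abstract, the opening of Section 3 and Section 3.2 also place adherence to the physiotherapy treatment, or the barriers to undertaking it, within the aim. Table 3, question 4, asks: "Was it easy or difficult for you to attend the treatment and evaluation sessions".

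Section 2.3 puts the subject more narrowly, as women's experience of following the advice and home exercises given by their physiotherapist.

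**The concern.** A study of why women do or do not adhere to a treatment needs to hear from some who did not. Here the supervised treatment is 12 sessions (Section 2.2.5), and completing all 12 is the entry condition. For that component, selection is on the very behaviour under study. A woman who found two visits a week unmanageable with a newborn, and stopped, is outside the sampling frame. More interviews inside the frame will not bring in her account.

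The Discussion says that the findings will help to design programmes that promote adherence and motivation. If reasons for missing or abandoning sessions come only second-hand, from women who managed to attend, such programmes may address the barriers that can be overcome and miss those that cannot.

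**Working it through.** The point rests on comparing the stated rule with the stated aim. The arithmetic only gives a sense of scale.

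**Step 1: split adherence into the parts the protocol mentions, and ask who can be heard on each.**

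| Part of the aim | Where stated | Can it vary among women who completed 12 sessions? |
|---|---|---|
| Attending and staying in supervised treatment | Abstract; Introduction; 2.3.2; opening of 3; 3.2; Table 3 question 4 | No. All eligible women completed it |
| Home exercises, habits, advice | 2.3; opening of 3; Discussion; Conclusions; Table 3 questions 5, 6 and 8 | Yes |
| Attending the evaluation visits | Table 3 question 4 | Yes. Visits run to 12 months after treatment |
| Self-efficacy and long-term maintenance | Abstract; Introduction | Yes |

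The conflict is confined to the first row. In that row completers can still describe difficulties that they overcame, and a woman whose sessions were postponed but who reached 12 remains eligible. What cannot be obtained is a first-hand account of missing sessions for good or of stopping.

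**Step 2: where the 10% comes from.** The qualitative study has no planned number of its own. The only dropout figure is in Section 2.2.2, for the randomised trial: difference 2.4 FSFI points, SD 4.5, two-sided alpha 0.05, power 0.80.

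- n per group = 2 × (1.960 + 0.842)² × 4.5² / 2.4² = 2 × 7.85 × 20.25 / 5.76 ≈ 55.2, rounded up to 56.
- With 10% dropout: 56 × 1.10 = 61.6, rounded up to 62; or 56 / 0.90 = 62.2, rounded up to 63.

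The stated 62 per group (124 in total) is therefore reproduced. The 10% is a sample-size allowance, and the article does not say when the losses are expected. Treatment lasts 6 weeks and follow-up a further 12 months.

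**Step 3: scale.**

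- Expected dropout at the planned rate: 0.10 × 124 = 12.4, about 12 women.
- If all of it fell in the treatment phase, about 12 would be barred from interview. If none did, dropout would bar nobody, because a woman lost after session 12 still meets the eligibility sentence. At the planned rate the range is thus 0 to about 12.
- If treatment-phase loss were instead 5% or 20% (assumed values, not in the article): 0.05 × 124 = 6.2 and 0.20 × 124 = 24.8, about 6 to 25.
- Women who stay in the trial but attend 11 or fewer sessions come on top. The article gives no figure for them.

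**The case against.** The strongest reply is that Section 2.3, which opens the qualitative methods, defines adherence as following advice and home exercises, and that the Discussion and Conclusions speak in similar terms. A woman can attend all 12 sessions and do no home training; she is eligible and non-adherent in that sense. Interviewing women months after treatment also suits an aim about long-term maintenance. This stands, and it limits the point. A reader might infer that every non-adherent woman is excluded, or that the second aim as a whole cannot be answered. The documents support neither.

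It does not remove the point. The Introduction names non-adherence to a treatment plan, Section 2.3.2 names adhering to a physiotherapy treatment, and the opening of Section 3 lists conservative treatment and home advice as two separate things. If only home adherence was meant, those statements are too wide.

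Three further inferences are tempting and should be left out:

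- That about 12 women will be excluded. This needs all dropout to fall within treatment, which the article does not say.
- That saturation will come too early because completers are alike. This is conjecture: the sample mixes two arms, two time windows, and individual and group interviews.
- That Table 3 by itself proves a contradiction. Question 4 also covers evaluation visits, and most of the guide can be answered fully by completers.

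It could also be said that the sentence on completion was meant only to fix the timing of interviews. As written it is a condition of entry, so it would need rewording in that case too.

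**Conclusion.** The point holds in limited form. The eligibility rule in Section 2.3.2 excludes women who were non-adherent to the supervised sessions, while the stated aim covers barriers to adherence, and non-adherence, to the treatment plan. Only the treatment-adherence part of the second aim is compromised. The parts on home exercises, advice, self-efficacy and maintenance can be studied among completers.

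The number excluded cannot be derived from the article. About 12 of 124 is illustrative, on the assumption that the whole 10% dropout occurs during treatment; women who remain in the trial but miss sessions would add to whatever the true figure is. The conclusion does not depend on that number, since the rule admits none of these women. The randomised comparison and its sample size are not affected. The change is worth making because it is cheap and serves one of the study's two declared aims.

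**What to change.** Preferred: in Section 2.3.2, replace the completion criterion with randomised women who attended at least one session. Alongside consecutive recruitment, purposively include women who missed sessions or withdrew and who agree to be interviewed. Redefine the two time windows so that they can be applied to a woman who did not finish, for example from her last attended session or from the planned end of treatment. Do not require saturation separately among non-completers: the group may be very small, and such a rule could keep the study from closing. Report how many were approached and how many agreed.

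Alternative: keep the criterion, and restrict the aim and the conclusions to adherence among women who completed treatment, in the Abstract, the Introduction, Section 2.3.2, the opening of Section 3, Section 3.2 and the Conclusions. State as a limitation that reasons for stopping are not heard first-hand.

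The preferred change costs one eligibility sentence, a consent line covering interview after withdrawal, and a few extra interviews by the same staff with the same guide. Its main weakness is that non-completers may be hard to reach and few may agree. The alternative costs only wording, but it gives up part of the second aim.
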